#### Cohort Study Target Population and Sample

Cohort participants were FSWs aged ≥18 years who live in Baltimore City; self-reported that they had traded sex for money, goods, or drugs 3 or more times in the past 3 months; and were not currently enrolled in our previous cohort study, the SAPPHIRE study [40]. Although transgender female sex workers (TFSWs) who reported being assigned male at birth were encouraged to visit the SPARC center and engage with peer outreach workers, they were excluded from the EMERALD study cohort because of a lack of comparable recruitment locations between the intervention and control areas.

Participants were assigned to a study arm based on the geographic location in which they were recruited. The initial target sample size was 350 women based on power calculations to observe a change in the intervention compared with the control group over the 3 follow-up visits. The assumptions used for the calculation were (1) n=200 in the intervention group and n=150 in the comparison group, (2) lost-to-follow-up (LTFU) rate of 10% to 20% in the intervention (effective n=160-180) and LTFU of 20% to 25% in the comparison group (effective n of 120-112), (3) intraperson correlation (Rho)=0.2-0.4, (4) varying levels of baseline risk behavior rate, and (5) a 2-sided α=.05. Thus, assuming effective sample sizes of n=160 in the intervention and n=112 in the comparison groups, the power is 83% to detect an odds ratio of 0.50, assuming a 20% prevalence rate of a risk behavior (eg, drug use) in the control group and an intraperson correlation of Rho=0.2. For the cumulative incidence outcome, with an average N contributing to the analysis of 170 in the intervention and 120 in the control groups, and assuming annual incidence rate of 6%, the power is 80% to detect a rate ratio of 0.28.

The enrollment target was increased to 450 midway through data collection after power calculations were reassessed based on actual retention rates within the sample, which were closer to 65%. The LTFU rate was higher than anticipated based on previous studies [41], likely because of high incarceration rates, the mobility of the population, and the length of time between study visits (6 months). Although we aimed for a sample of 450 participants, recruitment was stopped at 385 because of reaching saturation in the recruitment areas and repeatedly encountering participants attempting to reenroll in the study.

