#### Cohort Recruitment

EMERALD recruitment began 2 months before the opening of the SPARC center and took place from September 2017 to January 2019. The recruitment strategy for the EMERALD cohort was informed by SAPPHIRE, an earlier prospective cohort study of FSWs in Baltimore, conducted by this study team, which used targeted sampling [50]. Given that recruitment for SAPPHIRE concluded approximately 9 months before the launch of the EMERALD study, we conducted a series of geospatial analyses of possible sex work activity indicators using publicly available data [51] (eg, prostitution charge data and 911 call center reports of suspected prostitution) to understand possible shifts in the geotemporal distribution of sex work throughout Baltimore City (as compared with where we previously recruited FSWs in SAPPHIRE).

In total, the sampling frame for EMERALD consisted of 10 small geographic areas with high concentrations of sex work activity. Among them, 6 were located in the intervention area and 4 in the control area. Compared with our previous targeted sampling recruitment strategy among FSWs in Baltimore City [50], the time and day components of the sampling frame were selected based on analyses of time signatures associated with relevant secondary data in each location with high concentrations of sex work activity and supplemented with additional insights gleaned from SAPPHIRE. Before launching recruitment, staff conducted windshield tours in each location to confirm the presence of sex work activity.

A recreational vehicle (RV) retrofitted with 2 private interview areas and a bathroom for sample collection was driven to the field locations in the intervention and control areas 3 to 5 days per week depending on the interview volume. Each shift lasted approximately 4 hours at the recruitment site and was staffed by 1 field supervisor and 2 interviewers. A community advisory board made up of current and former sex workers provided input on all data collection strategies and instruments.

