For the primary biological endpoint of HIV and STI incidence, we will initially estimate cumulative incidence rates in both the intervention and comparison participants as a binary outcome and construct confidence intervals, accounting for the correlation structure because of nesting in geographic recruitment areas. The intervention’s effect will be assessed using an unadjusted random effect logistic model, with the intervention indicator as the only explanatory variable. The model will be expanded to include baseline covariates, such as demographic characteristics, history of sex work, and baseline risk behaviors (ie, condom use). A more detailed analysis will employ person-time methods with Poisson regression models to allow for time-updated covariates measured over time. Those lost to follow-up will contribute time-at-risk until the time of their last visit.

Finally, to evaluate the reach of the intervention, we will estimate SPARC involvement of FSWs in the independent cross-sectional survey at the 18-month follow-up period. We will also compare this sample with the FSW cohort at 18 months to assess their comparability or differences regarding demographic and risk profiles using logistic regression with group membership as the outcome variable.

To address aim 2, we will first describe changes over time in various sociostructural (ie, social cohesion and stigma) and structural vulnerability (eg, housing stability) indicators. We will then contrast these trends between the intervention and comparison groups. Social cohesion, social participation, and collective action will be analyzed as aggregate measures, the form of which will be determined by exploratory analysis. Specific models for formal statistical comparisons will be developed based on exploratory analysis, identifying both the distributional properties of the indicators and the shape of changes over time. To assess the association of these changes with the study’s primary endpoints, we will develop random effects logistic models, where the changes in structural indicators at each visit compared with baseline will be the main explanatory factors, in addition to the intervention indicator. The random effects will reflect the nesting of observations within the recruitment area and person over time.

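### The arm effect on HIV/STI incidence rests on 6 versus 4 areas; if the stated random-effect logistic model is read with large-sample inference, its nominal 5% error rate could reach about 10%

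*Protocol article*

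**What the plan says.** Under Cohort Study Target Population and Sample: "Participants were assigned to a study arm based on the geographic location in which they were recruited". Under Cohort Recruitment, of the 10 small areas in the sampling frame: "Among them, 6 were located in the intervention area and 4 in the control area". The significance level is "a 2-sided α=.05".

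For the primary biological endpoint, the Statistical Analysis section first estimates cumulative incidence by arm as a binary outcome and will "construct confidence intervals, accounting for the correlation structure because of nesting in geographic recruitment areas". The intervention effect then "will be assessed using an unadjusted random effect logistic model, with the intervention indicator as the only explanatory variable"; baseline covariates are added later.

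The section names no test (Wald, likelihood ratio or t), no degrees of freedom, no few-area correction and no between-area ICC. It rules none of these out. It also says that full analysis and power details can be requested from the senior author.

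**The concern.** Arm does not vary within an area, so the information on the arm effect is the difference between six area results and four. The random-effect model sees this correctly, but it must estimate the between-area variance from 10 areas, and large-sample inference then treats that estimate as known. Two things follow.

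- The critical value 1.96 is too small where 8 degrees of freedom apply.
- With 25 to 30 women per area the variance estimate often falls to zero, and the model then reports the standard error of independent women. In simulations with 251 women this happened in about 65% of runs at ICC 0.01 and 30-35% at ICC 0.05.

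At stake is whether a significant HIV/STI result reflects the intervention or a chance difference between two small sets of neighbourhoods.

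**Working it through.** **Inputs from the article.** Areas: 6 and 4. Level: 0.05, two-sided. Planned analysed numbers: 170 and 120, so 170/6 ≈ 28 and 120/4 = 30 women per area. Enrolled: 224 and 161. At the reported retention of about 65%, 0.65 × 224 ≈ 146 and 0.65 × 161 ≈ 105. Planning rate: 6% per year. The earlier Baltimore cohort described in the Background saw gonorrhea in 18.2% over 12 months.

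**Assumptions.** Between-area ICC of 0 to 0.10 on the logit scale (the article gives only a within-person correlation). Cumulative incidence over 18 months at two levels:
- planning rate: 1 − exp(−0.06 × 1.5) = 8.6%;
- earlier-cohort level: 18.2% × 1.5 ≈ 27% (at a constant hazard, 1 − 0.818^1.5 = 26%).

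**The plan's own power figure.** The article states: "assuming annual incidence rate of 6%, the power is 80% to detect a rate ratio of 0.28". Reading 6% as the mean of the two arm rates over 18 months, the control rate is 0.12/1.28 = 0.09375 and the intervention rate 0.28 × 0.09375 = 0.02625. Events are 120 × 0.09375 × 1.5 = 16.9 and 170 × 0.02625 × 1.5 = 6.7. The standard error of the log rate ratio is √(1/16.9 + 1/6.7) = 0.457, and |ln 0.28| = 1.273. Power is Φ(1.273/0.457 − 1.96) = 79.6%. The figure reproduces on that reading, and the calculation contains no between-area term.

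**Analytic check.** Degrees of freedom: 10 − 2 = 8. The t critical value is 2.306. Using 1.96 instead gives 2 × P(T₈ > 1.96) = 8.6%.

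**Simulation with no arm effect.** Normal area intercepts on the logit scale; random-intercept logistic model fitted by maximum likelihood with 25-point quadrature. Rejection rates in percent, 170/120 women, equal area sizes within arm, 4000 runs per row (Monte Carlo standard error at 10%: √(0.1 × 0.9/4000) ≈ 0.5 points):

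| Incidence | ICC | Wald z | Likelihood ratio | Same model, t on 8 df | Area-level t, 8 df |
|---|---|---|---|---|---|
| 27% | 0 | 4.5 | 4.1 | 1.8 | 4.8 |
| 27% | 0.01 | 6.1 | 5.1 | 2.4 | 4.3 |
| 27% | 0.02 | 7.4 | 6.5 | 4.0 | 5.0 |
| 27% | 0.05 | 10.0 | 8.2 | 5.6 | 4.8 |
| 27% | 0.10 | 10.1 | 7.6 | 5.7 | 4.2 |
| 8.6% | 0 | 3.6 | 3.9 | 1.5 | 4.8 |
| 8.6% | 0.01 | 3.9 | 4.4 | 1.5 | 4.5 |
| 8.6% | 0.02 | 4.6 | 4.9 | 1.6 | 5.3 |
| 8.6% | 0.05 | 5.4 | 5.5 | 2.5 | 4.4 |
| 8.6% | 0.10 | 7.3 | 7.1 | 3.2 | 4.6 |

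At 65% retention (146/105), 27% incidence, 2500 runs per row:

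| Area sizes | ICC | Wald z | Likelihood ratio | Same model, t on 8 df | Area-level t, 8 df |
|---|---|---|---|---|---|
| Equal | 0.02 | 6.1 | 4.8 | 2.4 | 4.2 |
| Equal | 0.05 | 8.8 | 7.4 | 4.8 | 4.4 |
| Equal | 0.10 | 10.8 | 8.4 | 6.3 | 4.8 |
| Unequal | 0.02 | 6.7 | 5.5 | 3.4 | 3.9 |
| Unequal | 0.05 | 9.8 | 7.5 | 6.2 | 4.1 |
| Unequal | 0.10 | 13.3 | 10.2 | 8.5 | 4.9 |

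A separately coded simulation put the Wald rate at about 4-7% for ICC 0.02 or below, 6-12% at 0.05 and 9-12% at 0.10, again with the area-level t test near 5%.

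**The case against.** The strongest reply is that this is silence in a condensed article. The text names a model family and accounts for nesting in areas; it never says that a Wald z test will be used. Degrees of freedom and small-sample corrections are commonly left to a fuller plan, and the article says fuller details exist. A reader might infer that the plan has no few-area correction and therefore runs at 10%. The documents do not support that: a correction is neither stated nor excluded, and 10% needs a Wald z test, an ICC of about 0.05 or more and incidence near 27%, all at once. At the article's own planning rate the Wald figure is 3.6-5.4% up to ICC 0.05 in the tabulated runs.

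Two other tempting readings also go too far. That the intervals for each arm's incidence will be too narrow was not tested, and the article gives no method for them. And permuting the 6/4 labels would not be an exact test: the areas were not randomised, and the intervention areas were chosen as one region, so the 210 possible splits (10 choose 4) were never equally likely.

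What remains is that the article does fix the model for the primary effect. With large-sample inference that model is anti-conservative once areas differ moderately. Adding degrees of freedom alone does not fully repair it: the same model referred to t on 8 df still reached 8.5% with unequal areas at ICC 0.10. The 27% level is also plausible, because the earlier cohort's gonorrhea rate alone leads to about 26% by 18 months.

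**Conclusion.** The point holds in conditional form. The comparison rests on 8 between-area degrees of freedom, and the article names a model without a few-area method. If that model is read with a Wald z or likelihood-ratio test, the nominal 5% would be:

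- about 4-7% at ICC 0.02 or below;
- about 10% for Wald at ICC 0.05-0.10 and 27% incidence, and up to about 13% with unequal areas at ICC 0.10;
- generally less at the planning rate, or with a likelihood-ratio test (about 4-8% at 27% incidence with equal areas, 10.2% at worst with unequal ones).

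The ICC, the area sizes and the choice of test are assumptions; the article gives none of them. If the full plan already uses a few-area reference, the point reduces to stating it.

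**What to change.** Base the primary p-value and interval for incidence on a few-area method. The preferred one computes each area's cumulative incidence (or log odds) and compares 6 areas with 4 by a t test on 8 degrees of freedom. For the adjusted version, fit the covariates without arm, form area residuals and compare those in the same way. Report the random-effect logistic odds ratio alongside, itself referred to t on 8 df. Any permutation of the area labels should be described as a sensitivity check, not as exact.

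The cost is a few lines of analysis-plan text and code. The drawback is precision: at a given standard error the t interval is 2.306/1.96 = 1.18 times as wide on the log scale, and some power is lost if the areas are truly alike.

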**Confounders**		
	**Housing stability**	
		Have you been homeless in the past 6 months?
		Where do you currently stay? Place that you own Place that you rent Family member’s place Shelter Transitional housing program Hotel or motel Streets, park, car, or abandoned building

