### Statistical Analysis

The principal analytic approach will center on generalized linear models for the individual data, with variance components that reflect the potential correlations among FSWs recruited from the same area and between repeated measurements from the same individual at baseline and follow-up visits [55,56]. The main covariate of interest is the intervention indicator. To address aim 1, we consider illicit drug use and irregular condom use as the primary behavioral endpoints.

The effect of the intervention will be assessed with a random effect hierarchical logistic model, with the intervention indicator, time, and their interaction as the main explanatory variables. To adjust for possible imbalances between the 2 areas, we will adjust for baseline confounding factors, including age, length of sex work, and number of sexual partners. The intervention effect will be assessed by comparing time trends in the intervention group with the time trend in the comparison group, as captured by the interaction term. The model will be expanded to include additional demographic covariates and time-dependent indicators of events such as arrest, homelessness, use of health services, or exposure to other prevention activities that are unrelated to the study. Aim 1 also seeks to evaluate the association between the degree of exposure to the intervention and observed behavioral changes. We will explore models that include as covariates participation or exposure to specific intervention components (ie, receiving medical care, drug treatment referral, and legal aid). On the basis of the literature, an 18-month follow-up should be sufficient to document meaningful changes in study outcomes, given the extent of the intervention [57].

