### Cohort Participant Characteristics

The final sample of the cohort (n=385) had a mean age of 37 years (SD 9.3 years), 56.6% (218/385) of participants were White, 70.9% (273/385) had attained less than a college education, and approximately two thirds of the sample (257/385, 66.8%) had a recent history of homelessness (Table 2). There were significant differences in racial categories between the intervention and control areas (*P*=.04). Women reported an average of 13 years (SD 9.5 years) in sex work. The prevalence of current substance use was high: 57.9% (223/385) injected any drug, 80.3% used heroin via any method, and 86.8% (334/385) used powdered or crack cocaine in the past 6 months. Almost half of the sample (174/385, 45.2%) reported a recent condomless sex with clients. HIV prevalence in the full sample was 5.2% (20/385), although only 3 women received new HIV diagnoses from study-related testing. Baseline gonorrhea and chlamydia prevalence were high at 15.8% (59/373) and 18.2% (68/374), respectively. There were no significant differences between the control and intervention groups in the key study outcomes at baseline.

**Table 2 table2:** Baseline characteristics of a sample of female sex workers in Baltimore, Maryland, recruited to the EMERALD (Enabling Mobilization, Empowerment, Risk Reduction, and Lasting Dignity) study (n=385).

Variables						Total (n=385)			Intervention (n=224)			Control (n=161)			*P* value	

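### The aim 2 association model names change from baseline but not the indicator's starting level; fitted that way it can dilute a real association or, if the starting level has its own lasting effect, reverse its sign.

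*Protocol article*

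**What the plan says.** The protocol article, Statistical Analysis, sets the aim 2 question and the type of model: "To assess the association of these changes with the study’s primary endpoints, we will develop random effects logistic models". It then names the terms: "where the changes in structural indicators at each visit compared with baseline will be the main explanatory factors, in addition to the intervention indicator". On correlation it adds: "The random effects will reflect the nesting of observations within the recruitment area and person over time". No aim 2 sentence mentions the indicator's level at baseline.

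For comparison, the aim 1 behavioural model is introduced "with the intervention indicator, time, and their interaction as the main explanatory variables", and the text then adds covariates: "we will adjust for baseline confounding factors, including age, length of sex work, and number of sexual partners". None of the baseline covariates named there is a structural indicator.

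Housing is one of the indicators. Table 1 gives the item "Have you been homeless in the past 6 months", a yes/no variable. The baseline results report that "approximately two thirds of the sample (257/385, 66.8%) had a recent history of homelessness".

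**The concern.** The question is whether changes in an indicator go with the endpoints. A change score on its own does not isolate that. A woman homeless throughout and a woman housed throughout both have change 0 and are treated alike. Only women homeless at baseline can improve, and only women housed at baseline can worsen, so change is negatively correlated with starting level. Any separate effect of starting level then enters the change coefficient with its sign turned round. The person random intercept does not remove this, because it is assumed independent of the covariates.

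At stake is the reading of the structural pathway. A real association with current housing could be understated. In one particular structure, gaining housing could look harmful when it does nothing.

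**Working it through.** **The plan's own figure.** The article gives no figure for the aim 2 model. Its behavioural power figure (83%, Cohort Study Target Population and Sample) belongs to aim 1. With 160 and 112 women, 20% against 11.1% (odds ratio 0.50), 3 visits and Rho 0.2, the variance factor is (1 + 2×0.2)/3 = 0.467 and power is 83.7%. It reproduces, but does not bear on this point. The tests below use the article's level, "a 2-sided α=.05".

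**What the named terms impose.** Let X0 be the starting level and Xt the level at visit t.

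- Change and arm only: logit p = a + b(Xt − X0) + arm. The effect of Xt is b and that of X0 is −b, so they are tied together.
- Baseline level added: logit p = a + b(Xt − X0) + gX0 + arm. The effect of Xt is b and that of X0 is g − b, so each is free.

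**Hand check for homelessness, first follow-up.** The 66.8% is from the article. The transitions (30% out of homelessness, 25% into it) are assumptions.

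| Baseline → visit | Share | Change |
|---|---|---|
| homeless → homeless | 0.668×0.70 = 0.4676 | 0 |
| homeless → housed | 0.668×0.30 = 0.2004 | −1 |
| housed → homeless | 0.332×0.25 = 0.0830 | +1 |
| housed → housed | 0.332×0.75 = 0.2490 | 0 |

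- Mean change = 0.0830 − 0.2004 = −0.1174.
- Variance of change = 0.2834 − 0.1174² = 0.2696.
- Covariance with starting level = −0.2004 + 0.668×0.1174 = −0.1220.
- Slope of starting level on change = −0.1220/0.2696 = −0.45.

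On a linear approximation, with ln 2 = 0.693:

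- Only starting level matters (odds ratio 2): −0.45×0.693 = −0.31, an apparent odds ratio of 0.73.
- Only current status matters (odds ratio 2): (1 − 0.45)×0.693 = 0.38, an apparent odds ratio of 1.46.

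**Simulation.** Person random-intercept logistic models, follow-up visits only, 3 visits, arm and visit included. The binary runs use 250 women (65% of 385) and an intraperson correlation of about 0.2; two separate runs were made. The continuous runs use 385 women with each visit observed with probability 0.65, indicator SD 1, between-visit correlation r of 0.3 to 0.7 and 400 replicates (Monte Carlo error up to 2.5 points). Entries are rejection rates unless marked.

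| What drives the endpoint | Change and arm only | Baseline level added |
|---|---|---|
| Nothing | 5.4% (binary), 3.0% (continuous) | 6.0%, 3.0% |
| Starting level, OR 2, binary | 46% and 52% | 6% and 7% |
| Starting level, OR 3, binary | 79% | 6% |
| Starting level, log-OR 0.2 / 0.4 / 0.6, r = 0.5 | 14% / 48% / 78% | 4.3% / 4.8% / 4.8% |
| Starting level, log-OR 0.4, r = 0.3 / 0.7 | 62% / 30% | 4.3% / 5.5% |
| Current status, OR 2, binary | OR 1.54, power 76%; OR 1.49, power 74% | OR 2.0, 96%; OR 1.95, 96% |
| Current level, log-OR 0.4, r = 0.5 | mean 0.23, power 69% | mean 0.41, power 98% |
| Stable trait only | 4.3% (continuous), 6% (250 women) | 39%, 42% |

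In the starting-level rows, every change-only rejection has the reversed sign. In the current-level rows of the continuous runs, no significant reversal occurs.

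**Baseline-visit rows kept (change = 0), r = 0.5.** Starting-level case: 13.5% / 35% / 64% change-only, against 5.8% to 6.5% with the baseline level. Stable-trait case: 5.5% against 29%. The pattern is the same and somewhat weaker.

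**Within-person version** (person mean plus deviation from it). Rejections stayed near 5% in both the starting-level-only and the stable-trait cases. Power when current status matters was about 77%, against 96% with the baseline level added.

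**The case against.** The strongest reply is that the article calls these the main factors of models still to be developed. Aim 1 uses the same word and then adds covariates. Where a closed list is meant, as in the first biological-endpoint model, the article says that the intervention indicator stands alone. It also says that full analysis details are held elsewhere. This stands in part. A reader might infer that the starting level is excluded; the text does not say so, only that it is not named. But the choice of change from baseline as the explanatory form is stated, and no sentence adds the level that this form needs.

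A reader might also infer that the model reverses signs in general. It does not. Reversal needs a starting level that acts in its own right while change has no effect, and nothing in the article establishes that. If current status matters, the sign is right and the estimate is diluted. If a stable trait drives the endpoint, change alone is near nominal and adding the baseline level is what produces false rejections. The Introduction's emphasis on lasting vulnerability makes that case relevant, so the baseline adjustment needs a companion check.

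A knock-on to the aim 3 mediation analysis might be inferred too. That analysis rests on a mediation formula and a causal mediation framework, not on change-score regressions, and is described as having limited power. The documents do not support carrying the problem over to it.

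**Conclusion.** The point holds in limited form. Fitted with the terms the article names, the aim 2 model ties the starting and current levels to equal and opposite effects, a restriction the article gives no reason for.

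- **Dilution:** if current status matters, an odds ratio of 2.0 is estimated at about 1.5 and power is about 75% instead of about 96%.
- **Reversal:** if only the starting level matters, the change coefficient is significant with the wrong sign about 50% of the time at a baseline odds ratio of 2, and 14% to 79% over the assumptions tried.

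The baseline homelessness rate, approximate retention, number of visits and Rho come from the article. The transition rates, between-visit correlations and effect sizes are assumptions, and the wide range reflects them. Aim 2 is an associational aim, and the aim 1 test of the intervention is untouched.

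**What to change.** In the aim 2 random effects logistic models, enter each indicator's baseline level together with its change from baseline (equivalently, baseline and current level). State that the change coefficient is conditional on starting level.

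Because that coefficient can reflect a stable unmeasured trait (about 40% rejections with no effect of change), also report a within-person version: the person mean and the deviation from it as separate terms. Take the mean over the follow-up visits being analysed, so that the deviations sum to zero within each woman and cannot carry a fixed starting level. Where the two models disagree, a stable trait is one explanation to consider.

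The cost is one extra covariate (one degree of freedom) per indicator, one sensitivity model and a few sentences in the analysis plan. No new data are needed. The within-person version is less powerful (about 77% against 96%), so it serves as a check and not as a replacement.
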